To test the primary research question, we will use regression model with the outcome Anxiety Level (AL) as dependent variable and condition (LTD vs WL) as predictor. Sex and Age will be added as extra predictors, plus interactions between predictors to see if the effects differ per sex and age category (LC). Model: AL = b0 + b1*Group + b2*Sex + b3*LC + b4*Group*Sex + b5*Condition*LC. To test the moderation and mediation models, we will use multilevel analysis [64]. The five assessments (T1,T2,T3,T4,T5) will be the lowest level, the children the second level. This model can be considered a moderated mediation model (Hayes, 2013). The mediation analysis will consist of 2 steps. 1st: Dysfunctional Cognitions (DC) and Avoidance Behavior (AB) will be dependent variables, in separate analyses. 2nd: Anxiety level (AL) will be the dependent variable. Time will be added and modelled as T = 0,1,2,3,4, to tested the linear increase of Anxiety Level (AL) during the intervention. We will use a random intercept model, because we expect individual differences to exist in the levels of DC, AB, AL. Step 1. DC = b0 + b1*Group + b2*Time VG = b0 + b1*Group + b2*Time. Step2. AL = b0 + b1*Group + b2*VG + b3*DC. To test the third hypothesis (moderation by cognitive level), we will perform a multilevel analysis as above. 1st: Dysfunctional Cognitions (DC) and Avoidance Behavior (AB) will be dependent variables, in separate analyses. Cognitive Level (CL) will be added as predictor in a hierarchical linear multilevel model, including the interaction with condition to test for the moderating effect of CL on the relation between condition and mediators. Time will be added and modelled as T = 0,1,2,3,4, to tested the linear increase of DC and AB during the intervention. We will use a random intercept model, because we expect individual differences to exist in the levels of DC and AB. DC = b0 + b1*Group + b2*CL + b3*Group*CL + b4*Time VG = b0 + b1*Group + b2*CL + b3*Group*CL + b4*Time. The variable Cognitive Level (CL) will be centered at zero. For the follow-ups, when interaction effects appear to be significant, simple slopes plots will be made to illustrate the interaction effect. The 95% confidence interval of the parameter estimates of the multilevel and logistic regression analyses will be used to assess the statistical and practical significance of the estimates. The standardized parameter estimates will be used as estimated effect sizes. For all interval variables univariate outlier detection will be applied by using the Inter Quartile Range (IQR): scores outside 1.5*IQR will be examined, in order to see whether these are genuine scores, and cannot be attributed to coding or other errors. If they are genuine the scores remain in the analysis, otherwise they are removed from the analysis. Since we will use multilevel analyses drop-outs can be kept in the analysis. Subjects with at least one wave (time point) with complete data will be used in the analysis. No imputation strategy will be applied. We will explore the time factor in more detail. Other coding schemes than a simple linear coding will be tested to see whether effect gradually weaken in time or take effect after a certain period. Furthermore, we will explore whether the proposed model has predictive value for the binary outcome (anxiety diagnosis).

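### Random-intercept-only models make the Step 2 mediator intervals modestly too narrow if both anxiety and the mediators drift within children; linear or late-onset Group-by-Time terms would suffer more

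*Protocol article*

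**What the plan says.** All of this is in the Protocol article, Analyses, unless stated otherwise.

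- Data structure: "The five assessments (T1,T2,T3,T4,T5) will be the lowest level, the children the second level".
- Random effects, mediation models: "We will use a random intercept model, because we expect individual differences to exist in the levels of DC, AB, AL". The moderation models repeat the choice: "We will use a random intercept model, because we expect individual differences to exist in the levels of DC and AB". Differences in level are the only reason given.
- Step 1: "DC = b0 + b1*Group + b2*Time VG = b0 + b1*Group + b2*Time". Step 2: "AL = b0 + b1*Group + b2*VG + b3*DC". VG stands where the text has avoidance behaviour (AB). No written equation contains a Group-by-Time term.
- Exploration of time: "Other coding schemes than a simple linear coding will be tested to see whether effect gradually weaken in time", or begin only after a delay.
- Inference: the 95% confidence intervals of the multilevel estimates decide significance. Robust standard errors are not mentioned.
- Schedule (Procedure; Intervention): waves follow sessions 1, 3 and 5 and the end of the eight-session training, then 12 weeks later. Sessions are weekly, with holiday breaks allowed.

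**The concern.** A random intercept captures stable differences between children. With independent residuals it leaves nothing else to link one wave to another, so waves two weeks apart are taken to be as closely correlated as waves twelve weeks apart.

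The article's own content makes that a strong assumption. The gaps are unequal. The section on the Learn to Dare study expects cognitive level to affect how far dysfunctional cognitions fall, and the Background says about a third of anxious children benefit too little from CBT. Both point to child-specific change.

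Step 2 regresses anxiety on time-varying cognitions and avoidance, and b2 and b3 carry the third and fourth aims (working mechanisms and their relative contribution). If outcome and mediator both drift within a child, neighbouring waves repeat part of the same information, but the model counts it as new. The intervals are then too short and a mediator path is declared too often.

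**Working it through.** **Inputs from the article.** 240 children, 120 per group; five waves; 10% drop-out between measurements; the equations above; two-sided 5% through 95% intervals. Weekly sessions give gaps of 3-1 = 2, 5-3 = 2, 8-5 = 3 and then 12 weeks.

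**Inputs assumed, because the article gives none.** ICC 0.5; AR(1) residual correlation 0.3 to 0.7 per wave; slope SD 0.1 to 0.3 per wave on a total SD of about 1.

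**The plan's own figure.** The stated 80% power at 240 comes with verbal effect sizes only. Simulated joint power for an indirect path runs from 37% to 90% over a-path d 0.2-0.3, b 0.10-0.14 and ICC 0.3-0.7 (81% at 0.3, 0.14 and 0.5). The figure is neither confirmed nor refuted, and the present point does not depend on it.

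**What the model implies.** With intercept variance τ² and residual variance σ², the correlation of any two waves is τ²/(τ²+σ²) = ICC. With AR(1) residuals it is ICC + (1-ICC)ρ^|j-k|. At ICC 0.5 and ρ 0.5 that is 0.5 + 0.5×0.5 = 0.75 for neighbouring waves and 0.5 + 0.5×0.5⁴ = 0.53 for T1 with T5. The random-intercept model fits one value to all pairs.

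**Simulation under no effect.** Random-intercept REML, monotone drop-out, about 2,000 trials per setting; Monte Carlo error √(0.05×0.95/2004) = 0.5 points.

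| Both anxiety and mediators generated with | Step 2 DC path | Linear Group-by-Time |
|---|---|---|
| Equal correlation | 4.5% | - |
| AR 0.3 / 0.5 / 0.7 | 5.9 / 7.3 / 9.2% | 10.1 / 13.5 / 17.4% |
| Slope SD 0.1 / 0.2 / 0.3 | 5.8 / 6.7 / 10.1% | 6.5 / 10.8 / 16.4% |
| AR and slopes combined | 11.4% | 20.2% |

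The ratio of model SE to true SD in Step 2 is 0.98, 0.93 and 0.87 for the three AR values and 0.82 for the combination. As a cross-check, a ratio r implies an error of 2[1-Φ(1.96r)]: r = 0.93 gives 6.8% and r = 0.82 gives 10.8%, in line with the table.

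**Where nothing goes wrong, or the error reverses.**
- Only anxiety serially correlated, mediators not: Step 2 error 4.8-4.9%.
- Group main effect: 4.2-5.6% in Step 1 and 4.0-5.3% in Step 2. Group*CL in the moderation models: 4.5-5.8%.
- Group-by-step from T3 or from T4: 8-17% in all but the mildest slope setting (5.7%). From T2: 4.2-9.6%.
- Group at T2 minus T1: 1.0-5.4%. Group at T3 alone: 1.7-5.4%. Here the SE can be too wide (ratio up to 1.27).

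**Repair.** The same fits with a child-clustered sandwich variance, A⁻¹(ΣsᵢsᵢᵀA⁻¹)·N/(N-1), where sᵢ is child i's score and A the model information; 4,000 trials per setting:

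| Setting | Step 2 DC path | Linear Group-by-Time | Group from T3 |
|---|---|---|---|
| AR 0.5 | 7.6 → 5.5% | 13.4 → 5.4% | 12.1 → 5.8% |
| Slope SD 0.2 | 6.1 → 4.9% | 11.2 → 5.1% | 8.8 → 4.9% |
| Both | 10.2 → 5.3% | 18.6 → 5.2% | 15.1 → 5.0% |

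**Sensitivity.** A repeat with 1,500 trials per setting gave 4.9-8.1% for the Step 2 path, 7-14% for linear Group-by-Time, and 4.5-6% with robust SEs. With ICC 0.6 the Step 2 path gave 5.3-7.7% for a single departure and 8.3% for slope SD 0.2 with AR 0.3. Adding Time to Step 2 leaves the result unchanged, so the absence of Time from that equation is a separate matter.

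**The case against.** The best case for leaving the plan alone has four parts.

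- **The Step 2 inflation is small and conditional.** This stands. The mildest settings (5.8-5.9%) lie less than two Monte Carlo errors above 5%, and the inflation vanishes if only anxiety drifts. A mediation claim also needs the a-path, which is correctly sized. With a true a of 0.35 SD, b of zero and both paths required, false positives were 4.4-6.0% under one departure and 7.5-9.3% under AR and slopes together.
- **The larger figures belong to models the article does not write.** This also stands. Group-by-Time enters only through the exploratory sentence, which has no equation.
- **The article is silent on residual covariance.** A detailed preregistered plan exists but is not shown, and it may specify that structure. Equal correlation therefore follows only with the usual independent residuals. Still, the random intercept, its levels-only reason and the use of model intervals are stated choices, not omissions.
- **Every magnitude is assumed.** True, which is why ranges are given.

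A reader might go further and infer that the Step 2 intervals are too narrow whatever the data look like, that every Group-by-Time coding is anticonservative, or that all the multilevel models need repair. None of these is supported: equal correlation gives correct error, some early or single-wave contrasts are conservative, and the between-child terms (Group, Group*CL) keep their nominal level.

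**Conclusion.** The point holds in a limited form. The stated random-intercept models fit poorly with the unequal wave spacing and the expected differences in change between children. If slopes vary or residuals are serially correlated in both anxiety and the mediators, type I error for b2 and b3 rises from 5% to about 5-8% for a single mild-to-moderate departure and to about 8-11% for strong or combined ones. Linear or later-onset Group-by-Time codings would run at about 7-20%, but these are exploratory.

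The conclusion rests on independent residuals in the fitted model and on assumed ICC, AR and slope values. It does not touch the Group comparison in Step 1 or Step 2, or the moderation test. It is a modest weakness in the mechanism analysis and cheap to remove.

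**What to change.** Keep the random-intercept models. State that the 95% confidence intervals for the Step 2 mediator paths, and for any Group-by-Time term examined when exploring time, use child-clustered robust standard errors (for example CR2). The plain sandwich form is what was simulated; with 240 children a small-sample correction should change little.

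A random slope for time, or a serial or unstructured residual covariance, can be added as a sensitivity analysis. These alternatives were not simulated, so they should not replace the robust intervals. Step 1 and the moderation models need no change on this account.

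The cost is a sentence of analysis wording and slightly wider mediator intervals. In the combined setting the model SE was about 0.82 of the true SD, so honest intervals would be about 1/0.82 = 1.22 times as wide; at AR 0.5 the factor is 1/0.93 = 1.08. No extra data are needed.

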### Participants

We aim at recruiting children aged 8–13 years with high levels of anxiety, specific phobias or other mild anxiety disorders that are included in the fifth edition of the Diagnostic and Statistical Manual of Mental Disorders (DSM-5): social anxiety disorder, separation anxiety disorder, generalized anxiety disorder, panic disorder, selective mutism, agoraphobia. With mild we mean that the disorder does not strongly interfere with daily functioning, or, in other words, does not have a high severity. By performing a simulation study with 500 replications [52] with the package “lme4” [53] in R (R Core Team, 2013), we calculated how many children from this population should be included in our sample. For this simulation we assumed a medium direct effect of the training, a small effect of the indirect pathways via the mediators and 10% random drop-out between measurements. To assess the effect of the intervention, we include a waitlist control group in addition to the intervention group. In order to obtain 80% power of the direct and indirect pathways, we need a total sample size of 240 (120 children in the intervention group and 120 children in the waitlist control group). In principle, the inclusion of participants will continue until we reach this number. We exclude children with severe anxiety diagnoses, as determined by a trained clinician during a diagnostic interview. No further exclusion criteria are applied. We will recruit our participants via the community (i.e., non-clinical/ non-refferred) in the Netherlands, a list of study sites can be obtained via the first author.

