Children in both groups perform the same assessments, which are all online within the ‘Learn to Dare!’ platform. Assessment points are aligned with the mediators, which means they take place before and after exposure and cognitive restructuring is offered to the children. At every assessment point child anxiety, avoidance behavior and dysfunctional cognitions are measured. The assessments are embedded in the intervention program, and take place after session 1 (after psycho-education and before the child’s expectancies are made explicit), after session 3 (before the start of actual exposures), after session 5 (before the start of cognitive restructuring), and at the end of the training. Control children receive automatically generated e-mails to notify them they have to complete an assessment. A follow-up assessment takes place 12 weeks after the last session. Both the intervention children and control children receive an automatically generated e-mail to notify they have to complete this assessment. At the follow-up assessment, the children take part in the diagnostic interview again. If children do not complete an assessment or intervention session, they will receive automatically generated reminders by e-mail twice. A research assistant also monitors the progress of the children and of the interviewers and trainers.

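### The mediator and moderation models have no Group-by-Time term, so their arm coefficients average over waves before the active ingredient and dilute a delayed effect

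*Protocol article*

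**What the plan says.** All references are to the protocol article.

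- **Mediator models (Analyses).** Dysfunctional cognitions (DC) and avoidance (written VG in the equations, AB elsewhere) are modelled as "Step 1. DC = b0 + b1*Group + b2*Time VG = b0 + b1*Group + b2*Time".
- **Moderation models (Analyses).** The DC equation is "DC = b0 + b1*Group + b2*CL + b3*Group*CL + b4*Time", and the one for avoidance has the same form.
- **Outcome model (Analyses).** The anxiety equation is "Step2. AL = b0 + b1*Group + b2*VG + b3*DC". It has no time term, so it does not supply the missing interaction either.
- **Data structure (Analyses).** "The five assessments (T1,T2,T3,T4,T5) will be the lowest level, the children the second level". Time is a linear main effect, "Time will be added and modelled as T = 0,1,2,3,4", with a random intercept.
- **Schedule (Procedure).** T1 follows session 1. T2 follows session 3 and is placed before exposure proper. T3 falls "after session 5 (before the start of cognitive restructuring". T4 is at the end of training and T5 is 12 weeks after the last session.
- **Aims (Learn to dare study).** Mediation is expected through decreases in dysfunctional cognitions and in avoidance. The Background section on exposure and cognitive restructuring treats change that occurs only after the ingredient has been given as a key prerequisite for studying mechanisms.
- **Power (Participants).** "In order to obtain 80% power of the direct and indirect pathways, we need a total sample size of 240". The simulation assumed a medium direct effect, small indirect effects and 10% random drop-out between measurements.

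**The concern.** With Group and Time entered only as main effects, b1 is one arm difference assumed equal at every wave. The schedule was built so that some waves precede each ingredient, yet those waves enter b1 as full outcomes. The coefficient cannot separate an arm difference already present at T1 from change after exposure or cognitive restructuring. If the effect starts late, b1 understates it. Group*CL in the moderation models is averaged over waves in the same way.

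The a-paths of both mediators and the test of moderation by cognitive level rest on these coefficients (aims 3 to 5). The risk is that a real mechanism is declared absent, or that a difference is credited to an ingredient without evidence that it followed it. The separate regression for the primary efficacy question is not affected.

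**Working it through.** **Inputs from the article.** 120 children per arm; five waves; 10% drop-out between measurements (Participants); T1-T2 before exposure and T1-T3 before cognitive restructuring (Procedure); random intercept and no Group-by-Time term (Analyses).

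**Assumptions, not in the article.** Intraclass correlation (ICC) 0.3 to 0.7; total variance 1; monotone drop-out, equal in both arms; the time course of the effect.

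**The plan's own figure.** The total of 240 cannot be reproduced. The article gives no numeric effect sizes, no ICC and no simulated model.

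**Formula.** With equal drop-out by arm, Group is orthogonal to Time, and the expected generalised least squares estimate is

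b1 = Σ p_k·S_k/(1+(k−1)·ICC) ÷ Σ p_k·k/(1+(k−1)·ICC)

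where p_k is the share of children with exactly the first k waves observed and S_k is the sum of the true arm differences over those waves.

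**Complete data.** Only k = 5 occurs, so b1 is the plain mean over waves:
- DC, full effect from T4: (0+0+0+1+1)/5 = 0.40.
- AB, full effect from T3: (0+0+1+1+1)/5 = 0.60.

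**With 10% drop-out, ICC 0.5.**
- p_1 to p_5 = 0.1, 0.09, 0.081, 0.0729, 0.6561.
- Denominator: 0.1×1 + 0.09×1.333 + 0.081×1.5 + 0.0729×1.6 + 0.6561×1.667 = 1.552.
- DC: S_4 = 1, S_5 = 2. Numerator 0.0729×1/2.5 + 0.6561×2/3 = 0.467. b1 = 0.467/1.552 = 0.301.
- AB: S_3 = 1, S_4 = 2, S_5 = 3. Numerator 0.081×1/2 + 0.0729×2/2.5 + 0.6561×3/3 = 0.755. b1 = 0.755/1.552 = 0.487.

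Drop-out worsens the dilution because the early waves are the most complete.

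**Share of the full effect recovered by b1:**

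| Assumed time course | Complete data | 10% drop-out, ICC 0.7 to 0.3 |
|---|---|---|
| DC, full from T4 | 40% | 29-31% |
| DC, half at T4, full at T5 | 30% | 21-23% |
| DC, half at T3, full from T4 | 50% | 38-41% |
| AB, full from T3 | 60% | 47-50% |
| AB, half at T3, full from T4 | 50% | 38-41% |
| AB, full from T2 | 80% | 70-73% |
| Linear divergence T1 to T5 | 50% | 40-42% |
| Constant from T1 | 100% | 100% |

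**Effect on power (illustration, assumed 0.5 SD, abrupt onset, 10% drop-out).** The standard error is √(2/(120 × denominator)); at ICC 0.5 it is √(2/(120×1.552)) = 0.104. For DC, b1 = 0.5×0.301 = 0.150 and power is 31%. Over ICC 0.3 to 0.7:
- b1: 25-41% for DC (onset T4) and 54-79% for AB (onset T3). If AB acts fully from T2, 86-98%.
- Group-by-wave contrast, T4 minus T1, arms not constrained at T1: 84-99%. With the arms constrained equal at T1 it is higher, but that constraint has to be stated and justified.

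**The case against.** - **The percentages depend on the time course.** This stands. A reader might infer that b1 recovers 30-50% of the effect as a fact about this trial. The documents do not say so: that range needs an abrupt onset, no earlier effect and monotone drop-out.
- **Exposure may change cognitions before T4.** This is fair. The Intervention section has the child state, rate, test and re-rate feared expectations during the exposure sessions, so some DC change by T3 is plausible. The dilution is then smaller but does not vanish.
- **Exposure may start before T2.** The Procedure section places T2, after session 3, ahead of exposure. The Intervention section describes the first experiment being carried out within session 3. The two must be reconciled; on the second reading AB recovery could reach 70-80%.
- **Other time codings will be explored.** The Analyses section wants to see whether the effect fades or starts late, and that question needs an arm difference that varies over time. But the work is exploratory and no interaction is printed. Recoding a main effect does not change b1. This is partial mitigation only.
- **The 80% power claim.** A reader might infer that it cannot hold. That is not shown. A constant effect of 0.2 SD gives b1 41-60% power, while 0.28 SD gives 68-87%, which spans 80%. Both effect sizes are assumed, because the article states none.
- **Equal time steps.** The 0 to 4 coding ignores the long gap before follow-up, and a reader might think this biases b1. It does not while Time is only a main effect and drop-out is equal by arm. It matters only once a linear Group x Time term is used.

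**Conclusion.** The point holds as a structural one. The printed Step 1 and moderation equations assume one arm difference, and one Group*CL coefficient, constant over T1 to T5. This conflicts with the article's own prerequisite for mechanism research, with aims framed as decreases, and with the assessment schedule. An effect that starts after T1 is diluted under every time course examined; only a difference constant from T1 escapes.

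The size is conditional. With an abrupt onset it is 40% (DC) and 60% (AB) recovered with complete data, or about 29-31% and 47-50% with the planned drop-out and ICC 0.3 to 0.7. Over the other time courses examined it is about 21-80%. The stated power for the indirect pathways can be neither reproduced nor refuted from the article.

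**What to change.** 1. Add Group x Time to the Step 1 models, and Group x CL x Time with its lower-order terms to the moderation models, preferably with wave as a categorical factor.
2. Name the confirmatory contrasts in advance as change from T1 to the first wave after each ingredient: AB at T3 and DC at T4. State whether the arms are constrained equal at T1, bearing in mind that T1 follows randomisation and session 1.
3. A linear Group x Time term is a workable alternative. If it is used, code time in actual weeks.
4. Reconcile the Procedure and Intervention sections on whether exposure begins before T2, since the AB contrast depends on it.
5. Check whether the power simulation used delayed effects with the model to be fitted. If it did not, rerun it and restate the power at 240.

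The cost is analysis-plan wording, possibly a rerun of an existing simulation, and a few more degrees of freedom. The stated power for the indirect pathways may come out lower. No new data are needed.

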CBT thus has a strong theoretical basis that is supported by empirical studies, convincingly demonstrating that CBT is currently an effective treatment for anxiety symptoms and anxiety disorders. To date, it is unknown whether CBT for children with anxiety actually works via decreasing dysfunctional cognitions and via decreasing avoidance. Studies on CBT’s working mechanisms in children are sparse. One of the most important prerequisites of examining working mechanisms is to establish that the outcome only changes after the active ingredients considered part of the working mechanisms has been offered [32]. This prerequisite is seldomly complied with. To our knowledge, mediation studies on child anxiety CBT are non-existent regarding online CBT and only a few mediation studies exist in which CBT was performed in a face-to-face format ([33]; P. C [34–37]). Of these face-to-face studies, only Hoogendoorn’s study (2014) meets the prerequisites of testing mediation [32]. Unfortunately, avoidance behavior was not taken into consideration in Hoogendoorn’s study. Therefore, we cannot draw firm conclusions on CBT’s effect on child anxiety via alteration of cognitions and avoidance behavior, and we cannot draw any conclusions about CBT’s working mechanisms when offered in an online format.

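### Step 2 of the mediation analysis regresses anxiety on raw same-wave mediator scores, so path b mixes stable differences between children with change within a child and carries no temporal order

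*Protocol article*

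**What the plan says.** The Analyses section describes a two-step mediation analysis in a multilevel model: "The five assessments (T1,T2,T3,T4,T5) will be the lowest level, the children the second level". The random part is a random intercept only: "We will use a random intercept model, because we expect individual differences to exist in the levels of DC, AB, AL".

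The first step is "Step 1. DC = b0 + b1*Group + b2*Time VG = b0 + b1*Group + b2*Time". The second is "Step2. AL = b0 + b1*Group + b2*VG + b3*DC". VG is not in the abbreviation list; I read it as avoidance behavior (AB).

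Immediately before these equations the prose says "Time will be added and modelled as T = 0,1,2,3,4, to tested the linear increase of Anxiety Level (AL) during the intervention". Time appears in both Step 1 equations and in both moderation equations, but not in Step 2. Centring is stated for one variable only: "The variable Cognitive Level (CL) will be centered at zero".

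Under Procedure, "At every assessment point child anxiety, avoidance behavior and dysfunctional cognitions are measured". No equation carries a lag or wave index. The Background (Exposure and cognitive restructuring) makes it a prerequisite of mechanism research that the "outcome only changes after the active ingredients considered part of the working mechanisms has been offered", and says earlier work seldom meets it. The third aim, under Learn to dare study, is worded in terms of decreases in the two mediators.

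**The concern.** A random intercept absorbs differences between children in the level of anxiety. It does not split the effect of a time-varying predictor. If children who are generally more anxious also generally avoid more and think more negatively, an uncentred mediator score picks up that stable association even when a change in the mediator does nothing to anxiety. Because mediator and outcome come from the same wave, and waves before the active ingredients are pooled with later ones, the coefficient also says nothing about order.

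If Time is left out as printed, any decline shared by the three scales adds to the same coefficient. What is at stake is aims 3 and 4 (whether, and how much, each mechanism carries the effect). A significant path b would be weak evidence for either, and the mediation result would then turn largely on path a.

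**Working it through.** **The plan's own figure.** The only stated figure is 240 children for 80% power on the direct and indirect pathways. It cannot be reproduced, because no numerical effects or variance components are given; that is not counted as an error here. A direct effect of 0.5 SD with 120 per arm has 97% power at one wave. At T5 it has 88%, with 120 x 0.9^4 = 79 per arm. Indirect power runs from 40% to 96% for path a of 0.20-0.28 SD, path b of 0.14 and an intraclass correlation of 0.1-0.7.

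**Inputs to the check.** From the protocol: 240 children, 1:1, five waves, 10% drop-out between measurements, random intercept, 95% intervals. Assumed, because the documents give none: trait and residual variance 0.5 each (intraclass correlation 0.5), trait correlations, common decline, treatment effects reaching their full size by T5. The true path b is 0 throughout.

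**Hand calculation** (one mediator, complete data, trait correlation 0.5, no decline, no treatment effect).
- Trait covariance: 0.5 x 0.5 = 0.25.
- Within-child slope: 0. Information per child: (5 - 1) x 0.5 / 0.5 = 4.
- Between-child slope: 0.25 / (0.5 + 0.5/5) = 0.417. Information per child: 5 x 0.6 / (0.5 + 5 x 0.5) = 1.
- Pooled slope: (4 x 0 + 1 x 0.417) / 5 = 0.083. Standard error: 1 / sqrt(240 x 5) = 0.029. z = 2.89.
- Chance of a significant b: Phi(2.89 - 1.96) = 82%.

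**Simulation.** Percentage of trials with a significant path b (200-500 replicates per scenario where recorded). Split means child mean plus within-child deviation. In the treated rows the effects on mediators and anxiety are independent, 0.5 SD each unless stated.

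| Scenario | As printed | + Time | + Time, split | + Group x Time, split |
|---|---|---|---|---|
| No treatment effect, decline or correlation | 6 | - | - | - |
| Treatment effects only | 13 | - | - | - |
| Trait correlation 0.5, no treatment effect | 80-83 | 83 | - | 3-6 |
| Common decline 0.5 SD, no treatment effect | 33 | - | - | 4-6 |
| Trait correlation 0.5, treated | 94 | 91 | 6 | 5 |
| Common decline 0.5 SD, treated | 94 | 7 | 7 | 5 |
| Both, treated | 100 | 91 | 11 | 7 |
| Milder: correlation 0.3, decline 0.3 SD, mediator effect 0.2 SD | 87 | 48 | 8 | 8 |
| Both, treated, plus same-wave state correlation 0.3 | 100 | 100 | 100 | 100 |

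In the two rows without treatment effect, the last column uses Group x categorical wave.

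**Declared mediation** (paths a and b both significant, model as printed): 48-49% in the last five rows other than the milder one that include a decline or trait correlation with treatment, 9% in the milder row, 5% when treatment does not move the mediators, and 88% with a mediator effect of 0.8 SD plus decline and trait correlation. In these scenarios the rate is at or close to that of path a alone.

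**Does a simple lag cure it?** Take avoidance at T3 predicting anxiety at T4, adjusted for anxiety at T3, with trait correlation 0.5. The correlations are 0.5 (anxiety T3-T4), 0.25 and 0.25. The partial slope is (0.25 - 0.5 x 0.25) / (1 - 0.25^2) = 0.133. With 240 x 0.9^3 = 175 children and R-squared 0.267, the standard error is sqrt(0.733 / (175 x 0.9375)) = 0.067, so z = 1.99 and the false-positive rate is about 51%. Simulation of such single-pair models gave 16-54% under trait correlation. Lagging deviations from the five-wave child mean gave 28% in the last row of the table, with a mean slope of -0.06 that is an artefact of the centring.

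**The case against.** Several points on the other side are sound.

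- A reader might infer that Time is simply absent. The prose says it will be added, and the printed equations are shorthand that also omit the random intercept. So this is a conflict between prose and equation, and Time does remove the common-decline problem (94% to 7%). It does not touch the trait component (94% to 91%, or unchanged at 83% without treatment effects).
- A reader might infer that the model will always report mediation, or that the hypothesis cannot fail. The documents do not support that: mediation also requires path a, and where treatment leaves the mediators alone the rate is about 5%.
- A reader might take regression to the mean after top-quartile selection as a built-in source of decline. Selection uses the YAM-5 at screening, and screening is not one of the five analysed assessments; the cognition and avoidance scales were not used to select. A decline across T1-T5 is an assumption.
- The assessments are aligned with the ingredients, which serves temporal order at the design stage, and other codings of time will be explored. Both stand, but Step 2 does not use the ordering, and recoding time does not lag a mediator.
- Detail may sit in the preregistered plan, which is not shown. That covers interval methods. It does not cover an outcome equation that the article itself prints in full.

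**Conclusion.** The point holds in this form. Step 2 as printed cannot distinguish stable between-child association from within-child change, and it tests no temporal order, contrary to the standard set in the Background and to the wording of the third aim. With a true path b of zero and an intraclass correlation of 0.5, path b is falsely significant in about 80-100% of trials at trait correlation 0.5. Including Time leaves about 83-91%, except where same-wave states also correlate, when it stays at 100%. A common decline alone gives about 33-94%, depending on whether treatment effects are also present, and Time cures that part.

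The sizes rest on assumed variances, correlations, trends and effects; the direction does not depend on their exact values so long as the traits correlate. False mediation can be declared when treatment moves the mediators; it is not inevitable. The efficacy comparison does not use Step 2 and is unaffected. Severity: should be fixed for aims 3 and 4.

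**What to change.** 1. In Step 2, include wave and Group x wave. This also settles the conflict between prose and equation.
2. Enter each mediator as the child's mean plus the within-child deviation, and take the within-child coefficient as path b.
3. In Step 1, define path a through Group x wave, naming the contrast, so that a and b refer to the same level.
4. Add, as a check of temporal order, a lagged model over all waves that separates stable child differences from within-child change, for example a random-intercept cross-lagged model. Do not rely on single wave pairs adjusted for prior anxiety, or on lagged deviations from the five-wave mean; both remain biased, as shown above.
5. State that same-wave estimates are associations, because same-wave state covariation still produces a false path b after the split.
6. Report a*b for each mediator with a Monte Carlo or bootstrap 95% interval.

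The cost is more modelling and wider intervals for the indirect effects. No new data, assessments or recruitment are needed.
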